### Design

We will adopt a simple, between-groups, four-arm prospective RCT design. Participants will be sampled from women who have failed to attend their recent appointment for breast screening. Women who have telephoned to decline or rearrange their screening appointment will be excluded. The intervention will be targeted at lower income women i.e. those from SIMD vigintiles 1–12.

The four treatment groups are: 1) Letter reminder (i.e. Treatment as usual: CONTROL); 2) Telephone reminder (TEL), 3) Telephone reminder plus telephone support (TEL-SUPP) and 4) Telephone reminder plus support plus AR (TEL-SUPP-AR).

#### Letter reminder group (CONTROL)

Participants randomised to the Control group will receive the reminder letter only, as current practice. This will be sent from the East of Scotland Breast Screening Centre.

#### All telephone groups (TEL, TEL-SUPP, TEL-SUPP-AR)

All telephone groups will receive the standard reminder letter in the same manner as the Control group. Participants in each of the three telephone groups will also be telephoned by the Research Fellow from the University of Stirling within two weeks of the reminder letter being posted. Telephone calls will be tape-recorded in order to check the fidelity of the intervention, and also to ensure accuracy of the participant’s answers recorded on the check-list. Participants who opt not to allow their calls to be recorded will still be able to take part in the intervention. Participants who do not answer or are not at home when telephoned, would be called on a maximum of 5 occasions, after which they would be recorded as non-contactable.

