### Informed consent

To preserve anonymity, no information will be given out about the nature of the phone call, until the Research Fellow is certain they are talking to the correct person. Verbal informed consent will be obtained at the beginning of the telephone support intervention, for those participants who affirm they are willing to be asked a few questions about breast screening. (Those who decline to answer any questions will be deemed to have refused consent and will not be contacted further.)

First, the purposes of the study will be read from a Patient Information Sheet. It will be made clear that the researcher is completely independent of the breast screening service and the participant's decision to participate (or not) will not affect their future treatment and that confidentiality of all their answers will be ensured. The participant will then be asked whether they consent to take part in the intervention.

Although we are not seeking written consent from intervention participants, patients' responses to the consent question will be recorded on a datasheet, and those refusing consent will be excluded from the study and will have no further contact from the researchers. Consent to tape-record the interview will also be sought; however, refusal to be recorded will not result in exclusion. Prospective participants who feel unable to decide immediately whether to take part will be given the option to be called back later, once they have had time to consider. They will also be referred to an independent researcher, if they would prefer to talk to someone else regarding the research. Participants who feel unable to decide will also be given the option of being posted the Information Sheet; and a follow-up telephone call will be arranged, to see whether they have decided to take part.

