Due to the design of our study, in which it is imperative that the telephone intervention is conducted as close to the posting of the reminder letters as possible to ensure parity of timing with the control and three telephone intervention groups, and to reduce the possibility that participants will already have rearranged their appointment before being telephoned, we are unable to seek written consent from participants. However, we believe that we have addressed any concerns about this by having the Research Fellow read the Information Sheet to all participants, as well as allowing prospective participants the opportunity to take time to reflect on taking part, speak to an independent person and/or to be posted the information sheet.

We are not seeking consent to collect follow-up attendance data from any participants for the following reasons: this would be impracticable for the control group; and for the three telephone groups, informing them that we would be checking their future attendance would in itself constitute an intervention, thereby confounding our true intervention, and precluding direct comparison with the control group. This would have the effect of rendering our results scientifically meaningless. Not seeking consent for collection of data on screening uptake is an approach previously used in a number of previous studies with cancer screening, all of which have gained ethical approval from UK National Health Service (NHS) Ethics Research Committees (i.e. colorectal cancer screening [15, 19]; cervical cancer screening: [13]).

We feel this approach is justified in the current research for the following reasons: (a) no harm will come to the participants from our collecting screening data, (b) our research cannot be practically carried out if we had to receive written informed consent from all participants, (c) the potential benefits to the NHS (i.e. determining effective methods of increasing breast screening in Scotland) outweigh any cost, (d) the East of Scotland Breast Screening Service already have access to the attendance data and (e) no individual identifiable results will be recorded in the database for analysis.

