#### Telephone support groups (TEL-SUPP and TEL-SUPP-AR)

Participants who are allocated to the telephone support intervention arms (TEL-SUPP and TEL-SUPP-AR) will be told that we are trying to understand why some women do not take up their invitation to attend for breast screening when invited and asked whether they would be prepared to answer some questions about breast screening. Those declining at this point would be assumed to have not given consent and would not be contacted further. The Patient Information Sheet will then be read out to prospective participants. This explains the nature and purpose of this research and reassures participants about the confidentiality and anonymity of their responses. They will be asked if they have any questions about our research and, if yes, will also be given the option of being able to talk to a Health Psychologist, who is independent of this research. They will be asked whether they agree to take part now (Yes/No), or whether they would prefer to be phoned back later.

In both telephone support arms (TEL-SUPP and TEL-SUPP-AR), patients will be asked to describe any reasons they had for not taking up the invitation to attend their appointment, and where appropriate, any barriers they mention will be addressed using a pre-specified list of responses, which will be generated from previous research (e.g. other women have mentioned that difficulty, but they managed to get over it by…. (How) could that work for you?’). Any patient queries or concerns about the process of breast screening will also be addressed, using responses from existing materials. Whether or not specific barriers are mentioned by individuals will be recorded on a check-list of barriers generated from the existing research and previous telephone interviews. Any additional barriers mentioned will be added to this check-list.

Participants in the TEL-SUPP and TEL-SUPP-AR groups would also be asked to say whether they now intended to make an appointment to attend for breast screening: ‘Do you intend to make an appointment for breast screening?’ ‘Yes’, ‘No’, ‘Maybe’ or ‘Don’t know’.

Participants will be reassured throughout that it is their choice whether or not to take up their invitation to attend breast screening, but that the researcher is there to seek their views on attending and to provide them with additional help and information, should they wish to make another appointment to attend.

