### Sampling and randomisation

Participants will be selected from those receiving an appointment for breast screening who do not telephone to cancel their appointment and who fail to attend or to re-arrange their appointment before the reminder letter is due to be sent. Sampling will be from the lists of women for whom reminder letters are generated. Postcodes will be used to derive Scottish Index of Multiple Deprivation (SIMD) vigintiles, and women who are from a SIMD vigintile between 1 and 12 inclusive (where 1 represents the most deprived areas), for whom telephone numbers can be obtained, will be randomised to treatment arm in a 1:1:1:1 ratio.

In order to achieve a balance between treatment groups, randomisation will be carried out by a member of the research team who is independent of the intervention on a record by record basis using minimisation via the MINIM software program [20] with age band (50–56, 57–63, 64 or older) and SIMD quintiles (i.e. 1, 2, 3 equivalent to vigintiles 1–4, 5–8 and 9–12) as the minimisation variables. The minimisation algorithm allocates the first record randomly and subsequent participants are allocated to minimise the imbalance between groups on the minimisation variables. It is currently the best available method of achieving randomisation whilst “ensuring excellent balance between groups for several prognostic factors, even in small samples” [21]. To ensure that the researcher does not influence the randomisation process, participants will be entered into the MINIM software sequentially, according to their order in the reminder letter list and the researcher will also remain blind to the identity of each treatment group (i.e. by randomising only to A, B, C, or D) during the randomisation process. The same researcher will collect the three-month follow-up data and carry out the data analysis and will continue to remain blind to the identity of each treatment group until this is complete.

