### Analysis

Our primary analysis will be chi-square to detect differences in the proportion of respondents who attended breast screening within 3 months of the reminder letter or call as a function of the 4 arms (control, TEL, TEL-SUPP or TEL-SUPP-AR). This will be followed by logistic regression of attenders versus non-attenders in the four groups, controlling for potential between-arm differences in age, social deprivation (SIMD) and history of previous breast screening attendance. Our primary analysis will be on an ‘Analysed as Allocated’ basis, i.e. including all participants, whether or not they were successfully contacted by telephone and/or agreed to take part in the study. Secondary analysis will be conducted for those agreeing to and participating in the intervention (TEL-SUPP and TEL-SUPP-AR groups only) to test the mediating and moderating roles of reported barriers, intention and AR in uptake of screening after reminder.

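### A booking made between the reminder letter and the call is not separated from stated intention, so the planned mediation and moderation analysis of intention could be confounded

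*Protocol article*

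**What the plan says.** The section on all telephone groups states that "All telephone groups will receive the standard reminder letter in the same manner as the Control group", and that the call follows "within two weeks of the reminder letter being posted". Women who do not answer "would be called on a maximum of 5 occasions, after which they would be recorded as non-contactable". Under Informed consent, women who cannot decide at once "will be given the option to be called back later, once they have had time to consider" or may be posted the information sheet, either of which can lengthen the gap between letter and interview.

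The same section gives a reason for calling promptly: "to reduce the possibility that participants will already have rearranged their appointment before being telephoned". The risk is therefore recognised, and the stated answer is to shorten the interval.

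Eligibility is fixed at the letter. Under Sampling and randomisation, the women selected are those who "fail to attend or to re-arrange their appointment before the reminder letter is due to be sent". The Design section also excludes women who telephoned to decline or rearrange. It gives no time point, but it does so while describing how participants are sampled.

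In the support arms women are "asked to say whether they now intended to make an appointment to attend for breast screening", with four permitted answers: Yes, No, Maybe, Don't know. The Analysis section then plans a secondary analysis, in women who took part in TEL-SUPP or TEL-SUPP-AR, "to test the mediating and moderating roles of reported barriers, intention and AR in uptake of screening after reminder". Under Primary and secondary outcomes, making another appointment is itself listed as a primary outcome.

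**The concern.** A mediator should be measured before the behaviour it is meant to explain. A woman who rebooks on receiving the letter and is then interviewed has already taken the main step towards attending. Her answer about intending to make an appointment is recorded afterwards, on a scale that does not fit her situation. Her existing booking influences both that answer and her later attendance, so it acts as a common cause of the two.

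At stake is the explanatory part of the trial: whether intention carries or modifies the effect on uptake, and whether asking about anticipated regret works through intention. If bookings made before the call are mixed in unrecognised, the estimated link between intention and attendance could be too strong, too weak or of the wrong sign. The data as collected would not show which.

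**Working it through.** **No figure to reproduce.** The protocol gives no share of women who rebook before the call and no sample size for the mediation analysis. The first step is therefore a reading of the text, and the second an illustration on stated assumptions.

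**Step 1: can a booking precede the measured intention?**
- The letter goes to all arms, and the call comes 0 to 14 days later. Repeat attempts and call-backs are allowed.
- Women who rearranged are removed as of the letter date. Reading the Design exclusion as applying after randomisation would conflict with the Analysis section, which keeps all participants as allocated.
- No section says that booking status is checked, dated or coded at the call.
- So yes: a booking made between letter and call can precede the intention answer, and such women stay in the secondary analysis.

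**Step 2: how large could the distortion be?** Let *R* = booked before the call, *M* = answered Yes to intention, *Y* = attended. The true effect of *M* on *Y* is set to zero.

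Assumptions, none from the protocol: P(Y) = 0.40 if not booked and 0.85 if booked; P(M) = 0.50 if not booked and 0.95 if booked; *R* from 0 to 30%.

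False slope of attendance on intention = (0.85 − 0.40) × [P(R | M=1) − P(R | M=0)].

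At *R* = 20%:
- P(R | M=1) = 0.19 / (0.19 + 0.40) = 0.322
- P(R | M=0) = 0.01 / (0.01 + 0.40) = 0.024
- slope = 0.45 × 0.298 = 0.134

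If booked women mostly answer No, with P(M | R) = 0.20 and *R* = 20%:
- P(R | M=1) = 0.04 / 0.44 = 0.091
- P(R | M=0) = 0.16 / 0.56 = 0.286
- slope = 0.45 × (−0.195) = −0.088

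The sign therefore depends on how a booked woman handles a question that does not fit her.

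**Step 3: the contrast between the two support arms.** A simulation (2,000 runs per setting, linear models) declared mediation when the arm-to-intention path and the intention-to-attendance path were both significant at 5%. It used 150 per arm (450 women / 3 telephone arms, if all take part) and 75 per arm (an assumed half). In the last two columns anticipated regret raises Yes answers by 20 points among women not booked (an assumption), and booked women mostly answer Yes.

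| Already booked | False slope, no AR effect (formula) | False mediation, 75 per arm | False mediation, 150 per arm |
|---|---|---|---|
| 0% | 0.00 | 3.9% | 4.5% |
| 5% | 0.039 | 5.2% | 7.8% |
| 10% | 0.073 | 8.1% | 16.0% |
| 20% | 0.134 | 15.6% | 38.0% |
| 30% | 0.183 | 21.0% | 54.4% |

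- With the 20-point effect and 20% booked, the simulated slope is 0.11 to 0.12. The false indirect effect averages 0.018 to 0.019, just under 2 percentage points of attendance.
- With **no** effect of anticipated regret on intention, the indirect effect averages zero and false mediation never exceeds 4.4%, because bookings made before the call are balanced between the randomised arms.
- Dropping women already booked (*R* = 20%, 20-point effect) returns the slope to −0.001 and false mediation to 3.0% (75 per arm) and 4.8% (150 per arm).

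**The case against.** The strongest reply is that the protocol sees the problem and limits it. Two weeks is an outer bound, calls are to be made as near to posting as possible, and sending the letter to every arm keeps the arms comparable. Rebooking before the call is described only as a possibility. Checklist coding and the definition of a secondary analysis set could sit in a full protocol, call script or SAP that is not shown.

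Much of this stands, and it rules out several stronger readings that a reader might infer:
- *That some women will have rebooked.* The text concedes a possibility and gives no rate.
- *That the analysis would show false mediation.* Between the two support arms the indirect effect is distorted only if anticipated regret also shifts intention, and the direction is not fixed.
- *That the barriers data are equally affected.* Women are asked for past reasons for missing the appointment, which predate the letter, so barriers are less exposed.
- *That the trial would credit the call with the letter's effect.* Both arms in this secondary analysis receive the support call, and intention is not collected in CONTROL or TEL, so it contains no call-versus-letter contrast.
- *That the primary result is biased.* Women can rebook before the call would be made in every arm, and all are analysed as allocated.

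The appeal to omitted detail does not dispose of the point. The intention question, its four answers and the set of women analysed are all stated. Followed as written, they mix women already booked with the rest. If booking status is not captured, a later analysis plan cannot recover it unless the screening database happens to hold the booking date.

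**Conclusion.** The point holds in a limited form. The protocol acknowledges that rearrangement before the call is possible, fixes an intention question with no answer for a woman in that position, and then analyses intention as mediator or moderator in all participating support-arm women. The intention–attendance path could be confounded in either direction.

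The size is unknown. Under the assumptions above, the false slope runs from about 0.04 at 5% already booked to 0.18 at 30% if booked women mostly answer Yes, and is about −0.09 at 20% if they mostly answer No. The elevated false-mediation rates further require a sizeable effect of anticipated regret on intention. That is an assumption, though a plausible one, since such an effect is part of any mediation of anticipated regret through intention.

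Only the secondary mediation and moderation analyses are affected. The change is worth making because it is cheap and must be in place before calls are made.

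**What to change.** - At the start of the support call, once consent is given, ask whether the woman has already rebooked. Code 'already rebooked' separately from the four intention answers. Confirm it against the booking date if the screening database holds one; the protocol does not say that it does.
- Keep every woman in the analysed-as-allocated primary analysis.
- Restrict the mediation and moderation analyses to women not rebooked at the call, or stratify by that status. The two support arms have the same contact until the anticipated regret questions near the end of the call, so status established at the start should not depend on arm, and restricting on it preserves the randomised contrast.
- Report the number and percentage already rebooked in each support arm.

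Cost: one extra checklist item, a sentence in the Analysis section and a somewhat smaller secondary-analysis set. Stratifying avoids the loss of numbers but leaves small strata if few women have rebooked.

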#### Telephone reminder group (TEL)

The telephone reminder (TEL) will be a simple telephone call to remind non-attenders that they did not attend their scheduled appointment and provide information on how they can rearrange this appointment. Women wishing to rearrange their appointment will be given the option of being transferred directly to the appointments service at the Breast Screening Centre in Dundee.

#### Telephone support groups (TEL-SUPP and TEL-SUPP-AR)

Participants who are allocated to the telephone support intervention arms (TEL-SUPP and TEL-SUPP-AR) will be told that we are trying to understand why some women do not take up their invitation to attend for breast screening when invited and asked whether they would be prepared to answer some questions about breast screening. Those declining at this point would be assumed to have not given consent and would not be contacted further. The Patient Information Sheet will then be read out to prospective participants. This explains the nature and purpose of this research and reassures participants about the confidentiality and anonymity of their responses. They will be asked if they have any questions about our research and, if yes, will also be given the option of being able to talk to a Health Psychologist, who is independent of this research. They will be asked whether they agree to take part now (Yes/No), or whether they would prefer to be phoned back later.

In both telephone support arms (TEL-SUPP and TEL-SUPP-AR), patients will be asked to describe any reasons they had for not taking up the invitation to attend their appointment, and where appropriate, any barriers they mention will be addressed using a pre-specified list of responses, which will be generated from previous research (e.g. other women have mentioned that difficulty, but they managed to get over it by…. (How) could that work for you?’). Any patient queries or concerns about the process of breast screening will also be addressed, using responses from existing materials. Whether or not specific barriers are mentioned by individuals will be recorded on a check-list of barriers generated from the existing research and previous telephone interviews. Any additional barriers mentioned will be added to this check-list.

Participants in the TEL-SUPP and TEL-SUPP-AR groups would also be asked to say whether they now intended to make an appointment to attend for breast screening: ‘Do you intend to make an appointment for breast screening?’ ‘Yes’, ‘No’, ‘Maybe’ or ‘Don’t know’.

Participants will be reassured throughout that it is their choice whether or not to take up their invitation to attend breast screening, but that the researcher is there to seek their views on attending and to provide them with additional help and information, should they wish to make another appointment to attend.

In order to check the acceptability and feasibility of the telephone support intervention, participants will be asked whether they minded being phoned up about breast screening, and also whether they found the telephone call helpful in addressing any concerns, queries or issues they might have regarding attending breast screening (‘Yes’, ‘No’, ‘Maybe’ or ‘Don’t know’).

It is envisaged each phone call would last 5–10 minutes, although some may take longer, if a participant has a lot of issues she wants to discuss, and some would be shorter, if the participant does not mention any barriers or does not wish to take part. Women who express a desire to rearrange their appointment will be given the option of being transferred directly to the appointments service at the Breast Screening Centre in Dundee at the end of the telephone intervention.

